### Explanation for the choice of comparators {6b}

In this trial, two presumably active groups are compared, the PMT group and the NVR group, against TAU. Parents in the TAU group will be offered to participate in PMT or NVR training in their respective inclusion centre after completion of the last study assessment.

### Objectives {7}

The main objective of this study is to assess the impact of non-violent parenting resistance training (NVR) and standard parenting management training (PMT) versus “usual treatment” (TAU) in improving irritability in children and adolescents with a baseline parent-rated affective reactivity index (P-ARI) greater than or equal to 4 in the context of ADHD, ODD, CD, mood / anxiety disorders or DMDD at 3 months after the program completion.

Main study hypothesis:

Both NVR and PMT are superior to TAU in improving irritability between baseline and 3 months after the program completion.

The secondary objectives of this study are:Assess improvement of irritability at different time-points (e.g., post completion).Assess improvement of irritability according to different informants (e.g., parents, child).Assess improvement of parental strategies.Explore putative mediators of therapeutic effect (e.g., parental expressed emotion, co-occurring disorders, personality).Assess acceptability of the interventions.

### Trial design {8}

The study described in this protocol is a prospective, multicentre, randomized (1:1:1), controlled superiority trial with evaluator blinding study conducted in France (Fig. 1).

**Fig. 1 Fig1:**
[figure not shown]
Flowchart. Flowchart of the RESIST RCT protocol testing the impact of non-violent parenting resistance training (NVR) and standard parenting management training (PMT) versus “usual treatment” (TAU) in improving irritability in children and adolescents with a baseline parent-rated affective reactivity index (P-ARI) greater than or equal to 4 in the context of ADHD, ODD, CD, mood / anxiety disorders or DMDD at 3 months after the program completion. N = planned/estimated sample size; M1 = at 1 month; M3 = at 3 months

## Methods

### Participants, interventions and outcomes

#### Study setting {9}

Patients are recruited at the child psychiatry units of the academic hospitals listed below. Study launching meetings are organized at each recruitment centre. Information (mailings, flyers, and posters) is distributed to partners of the different centres, including support groups, social services, and medico-social and associative structures. Clinicians of the participating centres are asked to screen their active files for eligible participants and to inform eligible parents and children about the RESIST RCT protocol. The study will then be presented to patients and their parents, along with appropriate information letters by the investigation team at the centre of Montpellier. If the patients/parents show interest in the study and give their consent a pre-inclusion visit is scheduled.

#### Eligibility criteria {10}

Inclusion criteria:

A subject has to meet the following criteria:Male and female subject between 6 and 15 years old.A confirmed K-SADS DSM-5 diagnosis of ADHD, ODD, CD, mood/anxiety disorder or DMDD. The request of a concomitant mental disorder allows to restrict this intervention to a clinical population.A parent-rated ARI total score of 4 or above at baselineA Clinical Global Impression-Severity score (CGI-S) of 4 or above (= at least moderately severe)Persistence of irritability symptoms 6 month or above at baseline (this avoids including children with transitory irritability)Stable treatment regimen (pharmacological and non-pharmacological) for 2 weeks prior to inclusion and during the trial

Exclusion criteria:

A subject will not be eligible for inclusion in this study if any of the following criteria apply:Unavailability of parents or legal representative during the study periodSubjects with a DSM-5 diagnosis (clinical presentation or history) that is consistent with Schizophrenia or psychotic disorders or acute manic episodes.Diagnosis of Autism Spectrum Disorder (ASD) in patients who are non-verbal and with IQ lower than 70Known or estimated IQ < 70 or clinical diagnosis of intellectual disabilitySubjects with severe irritability that are better accounted for by another factor, e.g., general medical condition(s) or direct effect of a substance (i.e., medication, illicit drug use), as determined by the clinical judgment of the investigator, or related to child abuse and/or neglectAbsence of informed consent form signed by at least one of the parents or legal representatives, and oral consent of the childInability to speak and comprehend FrenchDeemed unable to comply with the trial protocolParticipation in a structured parent program during the last 6 months

### Interventions {11a}

#### Standard PMT program

Our standard PMT program includes 10 online sessions and 2 booster online sessions, at 1 month and 3 months after completion. Sessions take place over two consecutive days.

Strategies for PMT group management are described in the manual book for clinicians:

Russel Barkley “Defiant children”, Guildford Press.

The session contents of the PMT program have been adapted to suit irritability and problematic behaviors and are described in the following section:First Session: Introduction about defiant disorders and irritability and presentation of participants (roundtable).Second Session: Psychoeducation about disorders associated with irritability including ADHD (Attention Deficit Hyperactivity Disorder), Oppositional Defiant Disorder (ODD), Conduct Disorder (CD), anxiety disorders, Autism Spectrum Disorders, Obsessive Compulsive Disorders, and Mood Disorders.Third session: Introduction to behavioural and cognitive therapy. Definition of operant conditioning and its impact in learning processes, including an explanation about the necessity of positive reinforcement of correct behavior.Fourth Session: Implementing a special time with the child, about 20 min daily, to get positive dynamics and share pleasant time.Fifth session: Learn to give effective orders, specifically adapting the way orders are given in order to increase the child’s compliance, e.g., avoid distractions, make orders as clear as possible, one order by time.Sixth session: Positive reinforcement of adaptive behavior. Parents learn to encourage their children when they display prosocial and adaptive behaviors in order to improve child’s autonomy, e.g., congratulating the irritable child as often as possible when he plays quietly or engages in cooperative attitudes.Seventh session: Set up a “point system” to increase the positive reinforcement’s impact and improve child’s motivation. Parents define positive behaviors that will be rewarded with special points. Accumulation of points may be exchanged against special non-material rewards.Eighth Session: Introduction to time-out periods. This strategy aims to face anger and temper outbursts in children.Ninth Session: Management of screens. Here we give strategies to set up a contract between parent and child to reinforce a controlled use of screens.Tenth Session: Management of schoolwork.

For the last five sessions, parents are separated into two groups: parents of adolescents and parents of younger children. The strategies used follow the same principles but are adapted to suit the age of the children (e.g., token reinforcement replaced by age-appropriate rewards).

Booster Sessions: review of strategies.

These sessions aim to review all strategies with parents, e.g., what was working or not, what limitations they had encountered, and what steps they could not overcome. Interactions between parents are very important at this stage because sharing their experiences is helpful for the entire group. Additionally, we can re-explain methods or strategies. We note that for many parents, time is necessary to understand the dynamics of parent management techniques.

#### NVR program

Our NVR program includes 10 online sessions and 2 booster online sessions (1 month and 3 months after completion). Sessions take place over two consecutive days.

The strategies for NVR group management are described in the manual book for clinicians:

[name], [name] “Accompagner les parents d’enfants tyranniques, un programme en 13 séances» Ed Dunod 2013.

The NVR Program differs to the standard PMT such that therapists never emphasize the behavior or reaction of the child but always the reaction of parents. During each session, the principles of Non-Violent Resistance are rehearsed: “Your child wants to prove to you that you cannot control him, but you have to show that you can control yourself, and that your behaviour does not depend on his behaviour. Your success is to control yourself and to use non-violent strategies, this is your only goal. The objective is to receive kindness from your child and not to change his / her behaviour. Of course, this is what you deeply wish, but if this may happen, it will be later … first you have to change and to persist”.

This is a crucial point, as therapists have to change the paradigm of objectives. It means for example, that when a parent is desperate because they have tried using a new strategy (like a sit-in) and must cope with a temper outburst more violent than ever, we consider the situation as a very positive occurrence, as long as parent managed to keep a non-violent attitude.

Every session is structured as follows. At the beginning, parents are invited to give feedback about what happened at home with their child during the last week, and what strategy they could use. Therapists reinforce parents to consider why they are able or not able to apply strategies. At the end, therapists present and explain a new strategy to use at home: most of the sessions are practical (e.g., write a declaration, to set up a sit-in) and some are more academic (e.g., describe the principles of NVR). Slides are used in order to clarify and to assist attention. After academic presentation, we ask to parents to react, e.g., “do you agree with our observations? Do you recognize the dynamic functioning of your family? Do you think it will be possible for you to use this strategy? What would limit you? What solutions could other parents find in this situation?” Often, when a parent feels trapped and overwhelmed, we ask for input from other parents in finding effective strategies.

First Session: Introduction.

This session is a presentation of the program, introducing what kind of violent or deviant behaviors children and teenagers may present at home and in the community. We explain that severe irritability includes temper outbursts and how it can impact family life and parental confidence. We present other types of violence that may be associated with severe irritability such as verbal violence to parents or others; physical violence; and psychological violence such as suicide threats, playing with parental guilt, etc. We let parents share their common feelings of shame, guilt, lack of parental confidence, and self-depreciation. At the end of the session, a roundtable is organized. This session may be very emotionally intense when parents talk about their child to strangers.

Second Session: Psychoeducation.

Here we explain how irritability can be determined in child development and the involvement of temperamental background and genetic factors. This explanation is also necessary for parents to understand that their child is not angry “after them” but that he/she has difficulties in regulation of emotions that impacts them first, as they are the closest caregivers.

We also include psychoeducation on disorders associated with irritability, e.g., ADHD (Attention Deficit Hyperactivity Disorder), Oppositional Defiant Disorder (ODD), Conduct Disorder (CD), anxiety disorders, Autism Spectrum Disorders, Obsessive Compulsive Disorders, and Mood Disorders.

Third Session: Introduction to Non-Violent Resistance.

Here we explain the historical and sociological background of NVR and its application in psychotherapy. We give an academic bases about the work of [name] who has developed specific programs to cope with violence in children and teenagers at home and in the community. This session also includes explanations about the New Authority approach and the role of social support. We present schematics of violence escalation and ask them to describe the process of violence and authority in their family. Most parents report scenes of escalated violence to try to face temper outbursts of their child, and how they felt guilty and incompetent after such experiences.

We teach NVR principles, e.g., “your enemy is violence, not your child”, “you must not win, but you must persist”, “you have to strike while the iron is cold.” We explain that their reactions have to be postponed and never impulsive. An educative response is much more efficient when it is postponed, and this is a way for parents to show to their child that they are not dependent on their own emotions and they are capable of controlling themselves.

Fourth session: Writing and reading a declaration of non-violence.

This session relates to the implementation of a change in parental attitudes. Here, parents must write a declaration to their child stating that they will no longer accept violence. They can give examples of two or three unacceptable behaviors of their child. This is not judging but only descriptive. For example, “We don’t accept that you hit your little brother when you are angry.” By the same way parents must also engage that they will no longer use violence against their child. They inform that they will do their best to find solutions, that they will not stay alone in this situation, and that they will ask to other people to help because this is the role of parenting.

Parents are asked to write a declaration for the next session, to read it to the child; if they do not feel ready, they can read it to the group before reading it to the child. We prepare them to potential reactions, but we insist on the fact that reaction of the child (positive or negative) is not our objective.

Fifth session: Finding social support and creating a support-group.

To increase their level of non-violent authority, parents must engage other people (e.g., friends, colleagues, family, other parents, teachers) that may constitute a support group. This forces parents to talk about their child’s behavior with someone, which can be a difficult step due to shame and guilt. However, parents experience that they can get support and people involved in a support group, which can reinforce their parental confidence. The objective of a support group is to talk with the child as often as violent behaviors happen. It means for the child that the behavior is not secret, that the parents are supported, and there is a social judgement regarding their behavior. A support group may also be called in case of violence or temper outbursts to assist the parents at home.

Sixth Session: Management of temper outbursts.

Here we provide an introduction to emotion regulation in children and adults, and how this regulation may be disturbed, e.g., how the child tries to cope with his own emotions and why it may explode. We describe processes of temper outbursts and why parents should not interact with their child during crisis. We give them strategies to face the crisis with the priority of protecting themselves. We talk about the involvement of a support group either by phone or in-person when it is possible (neighbors). It is most important to avoid escalations in violence, to search for help, and to call to emergency services if it becomes dangerous for the child or family. After this session, if they need, we propose they write an “emergency letter” for parents so that emergency workers (police, fireman, etc.) can get information about the situation for when they arrive at the home.

Seventh session: Sit-In.

A “sit-in” is a way to react “when iron is cold”; it means to react after a temper outburst or violent behaviors, when situation has calmed. Parents need to experience that they can still be in an authoritarian position even if they do not react immediately after a violent behavior. They just need to say to the child when the problem happens that they do not accept it and that they will think about consequences and come back later. Then they will have a couple of days of delay to come into the room of their child, sit, and say “We are here because we do not accept what happened last time (e.g., when you hit your brother) and we want you to find a solution.” Then they have to stay calm and silent for 30 min. They are instructed to leave if they do not feel safe (and come back another day with a member of the support group). This action shows their new position of authority and their determination. Parents sometimes feel afraid so they engage in role-playing during the session.

Eighth Session: Taking care of yourself.

When parents need to cope with irritability and temper outbursts of their child, it often takes a big place in their personal life; they always try to anticipate what could make their child angry, they try to avoid actions or words, they have the feeling of “walking on eggshells”. Finally, they also have a bad perception of themselves as parents and sometimes as people. They have the feeling that they have to do more for the child and family, and less for themselves. This may create conditions of anxiety and depression disorders, that may decrease their authority and their emotion regulation. That is why we insist on the necessity of taking care of themselves, e.g., do things they like, leave their home few hours or days, etc. These are actions of resistance. We also insist on the need to get medical help for themselves if they have symptoms of depression or sleep disorders. In this session we have a special time (about 30 min) for an introduction to mindfulness.

Ninth session: Increasing parental presence.

Most of the time, parents try to avoid their irritable child because their time together is unpleasant. The child may complain, show signs of anger and sadness, and try to transform family time into conflicts. We explain to parents that presence is now the key to authority, i.e., they must spend time with their angry child and show interest in their activities and friends. When a child/teenager is defiant and does not respect family rules, we ask parents to use a new strategy to increase their presence. For example, if the teenager breaks curfew, parents should contact as many friends as possible to give a “parental presence message” instead of trying to contact their child on their mobile phone (who will usually not answer). In this way, parents show the child that they are present. If their child is angry, they can simply say “it is my duty of mother to try to know where you are”. They increase their level of authority and this may convince their child to respect family rules in the future.

For the last five sessions, parents are separated into two groups: parents of adolescents and parents of younger children. The strategies used follow the same principles but are adapted to suit the age of the children (e.g., token reinforcement replaced by age-appropriate rewards).

Tenth Session: Management of screens.

This is a challenge for parents with irritable children because the interruption of screen activity may create a temper outburst. We discuss with parents’ different activities their child may engage in on the Internet. Parents need to manage the screen time with contracts, otherwise they can contact their support group to find solutions; when a contract is not respected, a 24-h total privation of screen time is recommended. When a child’s behavior is too violent, the help of the support group is requested.

Booster Sessions: review of strategies.

These sessions aim to review all strategies with parents, e.g., working or problematic strategies, limitations they had met, and steps they could not overcome. Sharing different experiences between parents is helpful for the entire group at this stage. For many parents, booster sessions can reveal that time is a necessary component to understand the dynamics of non-violence.

### Treatment as usual (TAU)

The TAU group receives non-pharmacological and pharmacological therapies as usually provided in the participating centres. The TAU group participates in the assessments as described in the procedures.

### Criteria for discontinuing or modifying the allocated interventions {11b}

Subjects may be withdrawn from the study at the discretion of the investigator or sponsor due to safety concerns. In addition, a subject must be withdrawn if one of the following applies:Subject chooses to withdraw from the study at any time.Major violation of the study protocol.Other circumstances that would endanger the health of the subject if he/she were to continue his/her participation in the trial.

Reasons for withdrawals and discontinuation of any subject from the protocol must be recorded.

The evaluation of protocol violations and patient removal will be produced only at the blinded data review stage.

Main major violations are:Participant did not complete a minimum of 50% of the program’s modules, including the follow-up visits.Participant did not complete the main study assessments.

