### Statistical methods

#### {20a}

A statistical analysis plan (SAP) will be prepared by the sponsor. Statistical analyses will be performed with SAS® version 9.4 or higher (SAS institute, North Carolina, USA).

Data will be analysed under the responsibility of the Unit of the Clinical research of CHU Montpellier with the SAS® software (SAS Institute, Cary, NC, USA).

The statistical analysis plan (SAP), covering all the analyses to be performed on all data, will be written before database lock.

Population sets

Four analysis, sets will be defined for this study:The Enrolled Set (ES) will include all subjects who sign an Informed Consent form.The Randomized Set (RS) will include all subjects who are randomized.The Full Analysis Set (FAS) will include all subjects who are randomized and have a valid primary efficacy measurement.The Per Protocol Set (PPS) will include all subjects who are in the FAS and who do not have an important protocol deviation that could affect the evaluation of the main outcome.

The FAS will be the primary set used for analyses/summaries of the primary efficacy variable, as well as for all secondary and other efficacy variables; the robustness of the analyses/summaries on the primary and key secondary efficacy variables will be assessed using the PPS.

The ES will be used for summarizing only the relative frequency of screen failures. The ES or RS will be used to establish the flow chart.

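### The mandatory-withdrawal rule in {11b} counts low module attendance, which can occur only in NVR and PMT, and conflicts with a primary analysis set that has no attendance condition

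*Protocol article*

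**What the plan says.** Four parts of the protocol article bear on this point.

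- **Criteria for discontinuing {11b}.** The section says that "a subject must be withdrawn if one of the following applies", and the list includes "Major violation of the study protocol". It then names two main major violations: "Participant did not complete a minimum of 50% of the program’s modules, including the follow-up visits" and "Participant did not complete the main study assessments". On timing it says: "The evaluation of protocol violations and patient removal will be produced only at the blinded data review stage". It does not say what a patient would be removed from.
- **Treatment as usual.** "The TAU group receives non-pharmacological and pharmacological therapies as usually provided in the participating centres". TAU families also take the study assessments, but they have no programme.
- **Population sets {20a} and Primary endpoint.** The FAS is every randomised subject with a valid primary measurement. "The FAS will be the primary set used for analyses/summaries of the primary efficacy variable", and the Primary endpoint section repeats this. Subjects with an important deviation leave only the PPS, which serves to check robustness.
- **Section {18b}.** For a withdrawn subject, the investigator should try to hold a final visit with the follow-up assessments.

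**The concern.** Read literally, {11b} turns low attendance into a compulsory exit from the study. Attendance is observed after randomisation, and the module criterion cannot be met in TAU. Any removal based on it therefore acts on two of the three arms, and on the families there who took up least of the programme. If such removal reached the primary analysis, families selected on attendance in NVR and PMT would be compared with unselected TAU families, and randomisation would no longer protect either contrast. In a superiority trial this favours the active arms if low attenders do worse than attenders.

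The way removal is decided adds a second difficulty. The Follow-up assessments section has the therapists of each treatment group record attendance. A reviewer who sees a module count knows that the family was not in TAU, so a review that applies this criterion is not blind to the contrast that the trial tests.

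**Working it through.** **1. The plan's own figures.** The Sample size section expects changes of −2, −2 and −0.5, with SD 3.
- The mean of the three is −1.5 and the deviations are −0.5, −0.5 and 1.0, so V = (0.25 + 0.25 + 1.0)/3 = 0.5, as stated.
- With 77 per group the noncentrality is 3 × 77 × 0.5/9 = 12.83. The one-way ANOVA then has 90.03% power, and 77 is the smallest n that reaches 90%.
- For dropout, 77/0.85 = 90.6, or 91 per group (273 in total). The stated 270 leaves 270 × 0.85/3 = 76.5 evaluable per group, which is close enough.

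These figures reproduce. They contain no allowance for low attendance and no estimate of it.

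**2. The texts side by side.**

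| Question | {11b} | {20a} and Primary endpoint |
|---|---|---|
| Does attendance below 50% matter? | Yes, a major violation with mandatory withdrawal | Not for the FAS; at most for the PPS |
| When is it judged? | At data review | Not applicable to the FAS |
| Which arms can meet it? | Modules: NVR and PMT. Missed assessments: all three | No arm-specific condition |

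Both instructions cannot be followed for a family with low attendance and a valid 3-month CL-ARI: {11b} removes it and the FAS keeps it.

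**3. When the trigger is known.** Table 1 puts all ten sessions on D1–D2. A family that attends none of them is already below 50%, however the denominator is read. Even if it then attends everything else, it reaches 0/10 on the sessions alone, 2/12 = 17% with both boosters, or 4/14 = 29% if V2 and V3 also count. Its status is thus settled about three months before the primary rating, although {11b} defers the formal judgement.

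**4. Size if removal did occur.** Let A be the mean change of attenders in an active arm, q the share of low attenders, and A + g their mean change (g points worse). The whole arm has mean (1 − q)A + q(A + g) = A + qg. Removing the low attenders leaves A, so the difference from TAU moves by −qg.

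For the two-sided type I error per comparison, assume no true effect and a gap g that is purely prognostic. Take 77 in TAU, 77(1 − q) in the active arm, SD 3 and a normal approximation. For q = 15% and g = 1.5:
- SE = 3 × √(1/77 + 1/65.45) = 0.504
- shift/SE = 0.225/0.504 = 0.446
- error = Φ(−1.96 + 0.446) + Φ(−1.96 − 0.446) = 7.3%

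| q (assumed) | g (assumed) | Shift | A difference of −1.5 would read | Type I error |
|---|---|---|---|---|
| 5% | 1 | 0.05 | −1.55 | 5.1% |
| 15% | 1.5 | 0.225 | −1.725 | 7.3% |
| 30% | 1.5 | 0.45 | −1.95 | 13.5% |
| 30% | 3 | 0.90 | −2.40 | 39.3% |

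Both q and g are assumptions; the article gives neither. If the FAS is applied as defined and the 3-month ratings are obtained, the shift is zero.

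**The case against.** The strongest reply is that the plan already does the right thing where it counts. The FAS has no attendance condition, it is named as primary twice, and deviations lead only to PPS exclusion. Section {11b} defers removal to data review, so it does not tell anyone to stop following a family. Its attendance item also mentions the follow-up visits, so for many families the count is not complete before V3. Section {18b} asks for a final visit even after withdrawal. The second violation, missed assessments, can occur in TAU as well.

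Most of this stands, and it rules out two stronger readings that a reader might infer.

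- **The primary comparison is already one of attenders against all of TAU.** The documents do not support this. It would require {11b} to override an explicit FAS definition, and nothing says that it does.
- **The effect would be overstated by 11% to 43%.** This follows from 1/(1 − p) − 1 for a non-attending share p of 10% to 30%, if non-attenders change like TAU and attenders by −2. The rates are not in the article, and the Sample size section gives −2 as the mean of each active group, not as the effect in attenders.

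The conflict itself is not answered. The wording in {11b} is mandatory, and removal is left without an object. The final visit in {18b} is a best effort, and a family without a valid rating leaves the FAS, with multiple imputation planned only as a sensitivity analysis under {20c}. How the data review is run may properly be left to the SAP, but a criterion that exists only in the active arms reveals active versus TAU however the review is organised. It need not reveal PMT versus NVR.

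**Conclusion.** The point holds as a contradiction within the protocol article that should be reconciled. It does not show that the primary analysis is biased. Section {11b} fixes an arm-dependent removal rule based on behaviour after randomisation, the FAS definition does not admit it, and no sentence says which prevails. Bias in both comparisons with TAU would arise on either of two conditions: {11b} is applied to the primary analysis, or withdrawal leaves the 3-month CL-ARI missing. Its size would be q × g, about 0.2 points on a planned difference of 1.5 in the middle of the illustrated range. The direction favours the active arms only if low attenders do worse, which is plausible but not stated. The asymmetry concerns the module criterion; missed assessments can occur in every arm. The matter should be settled before data review, because the choice could otherwise be made once attendance is known.

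**What to change.** Reconcile {11b} with {20a} and the Primary endpoint section:

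1. Remove protocol violation, and with it attendance, from the reasons for mandatory withdrawal from the study. Withdrawal for safety or at the participant's choice stays as it is.
2. State that attendance below 50% and missed main assessments affect PPS membership only, and replace the reference to patient removal with exclusion from the PPS.
3. State that every randomised family is followed to V2 and V3, whatever its attendance, and analysed in the arm to which it was randomised.
4. Say openly that the PPS review, where it uses module counts, is not blind to active versus TAU.

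This is a change of wording. The V2 and V3 assessments are remote and already scheduled for all arms, so the added cost is the effort to rate families who stopped attending. The downside is a possibly smaller estimated effect, since families with little exposure to the programme remain in the comparison.
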